## Abstract

**Background:**

A major challenge to psychological treatment for alcohol use disorder (AUD) is patient non-compliance. A promising new treatment approach that is hypothesized to increase patient compliance is blended treatment, consisting of face-to-face contact with a therapist combined with modules delivered over the internet within the same protocol. While this treatment concept has been developed and proven effective for a variety of mental disorders, it has not yet been examined for AUD.

**Aims:**

The study described in this protocol aims to examine and evaluate patient compliance with blended AUD treatment as well as the clinical and cost effectiveness of such treatment compared to face-to-face treatment only.

**Methods:**

The study design is a pragmatic, stepped-wedge cluster randomized controlled trial. The included outpatient institutions (planned number of patients: *n* = 1800) will be randomized in clusters to implement either blended AUD treatment or face-to-face treatment only, i.e. treatment as usual (TAU). Both treatment approaches consist of motivational interviewing and cognitive behavioral therapy. Data on sociodemographics, treatment (e.g. intensity, duration), type of treatment conclusion (compliance vs. dropout), alcohol consumption, addiction severity, consequences of drinking, and quality of life, will be collected at treatment entry, at treatment conclusion, and 6 months after treatment conclusion. The primary outcome is compliance at treatment conclusion, and the secondary outcomes include alcohol consumption and quality of life at six-months follow-up. Data will be analyzed with an Intention-to-treat approach by means of generalized linear mixed models with a random effect for cluster and fixed effect for each step. Also, analyses evaluating cost-effectiveness will be conducted.

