### Data collection

All patients from each of the participating treatment institutions will be followed up in the National Register of Alcohol Treatment (NAB). In accordance with Danish Law, this register contains data on all patients receiving publicly funded treatment for AUD. The register provides data on sociodemographic characteristics, compliance, and alcohol related variables (see Table 1).

**Table 1 Tab1:** Data collected during the BLEND-A study

Domain	Measure/source	Content	Reference	Time-point
Descriptive variables				
Sociodemographics and treatment data	National Alcohol Treatment Register (NAB)	Gender, age, education, etc. and treatment duration and intensity as well as prior treatment.	[51, 52]	Treatment entry and treatment completion
Primary outcomes				
Compliance	National Alcohol Treatment Register (NAB)	Treatment retention and type of treatment conclusion (i.e. dropout or completion).		Registered on continuous basis in the national register
Secondary outcomes				
Alcohol consumption	Alcohol Use Disorders Identification Test (AUDIT)	Items from the AUDIT: Quantitiy/frequency measure of alcohol consumption.	[53]	Treatment entry and 6-month follow-up post treatment
AUD severity	Alcohol Use Disorders Identification Test (AUDIT)	AUDIT asesses AUD, alcohol consumption, drinking behaviors, and alcohol-related problems	[53]	Treatment entry and 6-month follow-up post treatment
	Alcohol Dependence Scale (ADS):	ADS measure the severity of alcohol dependence symptoms.	[54, 55]	Treatment entry and 6-month follow-up post treatment
	Short Inventory of Problems-2 Revision (SIP-2R)	SIP-2R evaluates alcohol-related problems.	[56]	Treatment entry and 6-month follow-up treatment
	National Alcohol Treatment Register/ Addiction severity Index (ASI)	ASI assesses multidimesional addiction severity related to various domains: alcohol and drug use, physical and mental health, employment, legal problems and social functioning.	[51, 52]	Treatment entry and treatment conclusion
Quality of life	European Quality of life - 5 Dimensions (EQ5D)	EQ5D evaluates quality of life on five dimensions: mobility, self-care, usual activities, pain/discomfort, and anxiety/depression.	[57, 58]	Treatment entry and 6-month follow-up post treatment.
Usability of blended treatment	System Usability Scale (SUS)	SUS evaluates the usability of the web-based treatment system.	[59]	6-month follow-up post treatment.

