Institutional level data will cover 1 year before treatment start until the end of the study period for all consecutive patients at the participating treatment institutions.

In addition to the register data, all patients seeking treatment at the participating treatment institutions during the study period will be asked to complete a questionnaire at treatment start and after treatment completion 6 months later. The questionnaire will consist of questions on the patients’ contact information, alcohol consumption, consequences of drinking, quality of life and usability of the internet-based platform (see Table 1).

The questionnaire will be administered via tablets at the treatment institutions or by secure mail or telephone interviews conducted by blinded research assistants. If a patient stops treatment before the 6 months follow up, the questionnaire will be emailed to him/her via a safe link or administered over the phone by a researcher. The questionnaire-based data will be collected from patients in both the intervention and the control groups. Data will be collected using REDCap™ (Research Electronic Data Capture), which is a secure web application for building and managing online data entry systems [60], and stored in OPEN, Open Patient data Explorative Network, Odense University Hospital, Odense. Data on use of the BLEND-A modules will be obtained from the platform.

Randomly chosen patients and therapists will be asked to participate in additional qualitative interviews, conducted either individually or in focus groups to investigate how participation in blended care is experienced by the users. An interview guide will be developed, which will allow the patients and therapists to describe both the challenges and opportunities associated with the blended treatment approach [61].

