### Data analysis

In a stepped wedge study, the distribution of results across unexposed observation periods is compared with the distribution of results across the exposed observation periods [62]. The data in the present study will be analyzed using an Intention-to-treat approach and by a blinded statistician. In the BLEND-A study, the evaluation will be conducted over a 16-month period during which the proportion of clusters exposed to the blended treatment intervention gradually increases. Adjusting for the systematically different observation periods and for clustering in the data will be accomplished by fitting an appropriate generalized linear mixed model or using generalized estimating equations (GLMM). We may also decide to examine how the impact of implementing blended treatment develops (over time) once it is introduced into a cluster, since the intervention may need an initial period of adjustment before becoming fully embedded in the setting. Hence, the length of the period (up to the current observation) during which the cluster (treatment institution) has been exposed to the intervention may be included in the model as an effect modifier [62].

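### The model named for the secondary outcomes includes no patient entry value, although the same instruments are collected at entry; adding it would gain precision at almost no cost

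*Protocol article*

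**What the plan says.** The abstract of the protocol article lists the primary and secondary outcomes ("the secondary outcomes include alcohol consumption and quality of life at six-months follow-up") and then gives the analysis as "generalized linear mixed models with a random effect for cluster and fixed effect for each step".

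The Data analysis section is more open: "Adjusting for the systematically different observation periods and for clustering in the data will be accomplished by fitting an appropriate generalized linear mixed model", with generalized estimating equations as an alternative. The only further term it raises is the length of time a cluster has been exposed, as a possible effect modifier.

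Table 1, under Data collection, describes the consumption measure as "Items from the AUDIT: Quantitiy/frequency measure of alcohol consumption" and states that "EQ5D evaluates quality of life on five dimensions". The time points for AUDIT, ADS and EQ-5D are "Treatment entry and 6-month follow-up post treatment", and SIP-2R has an equivalent entry. The text below the table says that all patients are asked to "complete a questionnaire at treatment start and after treatment completion 6 months later". A same-instrument entry value is therefore planned for each of these outcomes.

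**The concern.** A patient's entry score is usually among the best predictors of the later score on the same scale. A model with only period and cluster terms leaves that predictable part of the patient-level variation in the residual. In a stepped wedge the treatment contrast comes from fairly small institution-by-period cells, where patient-level variation makes up much of the standard error.

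The outcomes concerned carry the second and third hypotheses (alcohol consumption and quality of life). The article expects only 25-40% of patients to take up blended treatment, so intention-to-treat effects will be diluted and precision matters.

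There is also a reason beyond precision. Patients enrol after their institution has been randomized, and the Discussion reports that in the pilot some patients came specifically because internet-based treatment was on offer. Entry drinking or quality of life may therefore differ between exposed and unexposed periods. Step and cluster terms do not remove such a shift. Conditioning on the entry value deals with the part of it that is measured.

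**Working it through.** **The plan's own figure.** The article gives no power, SD, intra-cluster correlation or entry-to-follow-up correlation for any secondary outcome, so there is nothing to reproduce. Its one power statement (31% against 41%, at least 80%) concerns treatment completion, which has no patient-level entry value.

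**Inputs from the article.** 1800 patients; 18 institutions in four waves (Study procedure and randomization), or 8 centres, two major with typically 300-600 new patients a year and six minor with 60-80 (Power calculations); two-sided 5% level.

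**Assumptions.** Five periods with the first all control; either 18 equal institutions split 5/5/4/4 over the waves, or 8 unequal centres with relative sizes 450, 450 and six of 70, two per wave; 100% or 60% follow-up; total variance 1; ICC 0.01 or 0.05; cluster autocorrelation (CAC) 1 or 0.8; linear model; entry-to-follow-up correlation ρ from 0.3 to 0.7.

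**Formula.** The variance of the treatment effect is the generalized least squares variance with fixed period effects. The cell means of one institution have a shared variance ICC × CAC, a cluster-period variance ICC × (1 − CAC), and a patient part (1 − ICC)/m, where m is the cell size. Adjustment for the entry value multiplies the patient part by (1 − ρ²). The between-cluster parts are left unchanged, which is the cautious choice. If they shrank in the same proportion, the gain would be exactly ρ².

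**One case in numbers.** With 18 equal institutions and full follow-up, m = 1800/(18 × 5) = 20. At ICC 0.05 and CAC 0.8:
- patient part unadjusted: 0.95/20 = 0.0475
- patient part at ρ = 0.5: 0.0475 × 0.75 = 0.0356
- cluster-period part: 0.05 × 0.2 = 0.0100
- independent noise per cell: 0.0575 falling to 0.0456, a fall of about 21%

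The full calculation, which also carries the shared cluster part, gives a fall of 18.9%. An effect with 80% power unadjusted lies 1.960 + 0.842 = 2.802 standard errors from zero. After adjustment this is 2.802/√(1 − 0.189) = 3.111, and the power is Φ(3.111 − 1.960) = 87.5%.

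**Range over all the combinations above.**

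| ρ | Fall in variance of the effect | Power where it was 80% |
|---|---|---|
| 0.3 | 5-9% | 82-83% |
| 0.4 | 10-15% | 84-86% |
| 0.5 | 15-24% | 86-90% |
| 0.7 | 31-48% | 92-97% |

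The lower ends come from the 8 unequal centres with ICC 0.05 and CAC 0.8. With 18 equal institutions the fall at ρ = 0.5 is 19-23%.

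**Raw change is no substitute.** Relative to the follow-up score, the patient-level variance of a change score is 2(1 − ρ), and that of the entry-adjusted score is 1 − ρ²:
- ρ = 0.3: 1.40 against 0.91
- ρ = 0.5: 1.00 against 0.75
- ρ = 0.7: 0.60 against 0.51

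At ρ = 0.5 a change score gains nothing over the follow-up value, and below that it is worse.

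**The case against.** The strongest reply is that the article does not fix a covariate list. The abstract line is a summary and does not even name the intervention term, so it cannot be the full model. The Methods text speaks of "fitting an appropriate generalized linear mixed model or using generalized estimating equations". Covariates for secondary outcomes are commonly left to an analysis plan or full protocol, and neither is shown. This largely stands. A reader might infer that the plan limits the model to cluster and step, but the article does not say so. What remains is that the two places describing the model name period and clustering and no entry value, so an analysis that followed them literally would give up precision.

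A reader might also take a fixed loss, such as a fifth of the variance, as established. The documents do not support that. One fifth corresponds to ρ of about 0.45 if the gain is ρ², and no correlation is stated. A lower value is plausible: Table 1 places follow-up 6 months after treatment and usual treatment typically lasts 4 to 6 months, so the two measurements could be 10 to 12 months apart, whereas the hypotheses count 6 months from intake. At ρ = 0.2 the fall is only about 2-4%. At ICC 0.10 with CAC 0.8 and 8 unequal centres, the fall at ρ = 0.5 is about 13%.

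The factor (1 − ρ²) belongs to a linear model. The AUDIT quantity and frequency items are ordinal and the link is left open, so the figures are a guide for those items.

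Finally, it is tempting to extend the point to the QALY comparison. The article treats the economic analysis separately and does not describe a model for the QALY difference, so it cannot be said that entry EQ-5D is left out there.

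**Conclusion.** The point holds as a low-cost improvement for the secondary outcomes measured at entry. The named model includes no entry value although the data will exist, and adding it gives a more precise estimate and some protection against a measured change in case mix. It is not a contradiction in the plan, and it does not touch the primary outcome.

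The gain depends on a correlation that the documents do not give. It is modest at 0.3, about 2 to 3 points of power from a base of 80%. It is worth having at 0.5, about 6 to 10 points. These figures rest on the layouts, ICC, autocorrelation and follow-up rates assumed above. Whether the gain would decide the detection of a real effect cannot be said, because no target effect is stated for these outcomes. The case-mix argument is qualitative: the pilot observation makes a shift possible but does not show its size.

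**What to change.** State in the analysis section or the analysis plan that, for each secondary outcome measured at entry (AUDIT consumption, AUDIT total, ADS, SIP-2R, EQ-5D), the model for the follow-up value contains that patient's own entry value of the same measure as a fixed covariate, beside the intervention, step and cluster terms. State that neither the unadjusted follow-up value nor raw change alone will be the main analysis. Say how missing entry values are handled, for example by modelling entry and follow-up values jointly.

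As a suggestion only, the QALY difference could be adjusted for entry EQ-5D in the same way.

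The cost is a sentence or two, with no new data and no further patients. The one added burden is the handling of missing entry scores. The wording should be settled before outcome data are examined.

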**Discussion:**

Blended treatment may increase treatment compliance and thus improve treatment outcomes due to increased flexibility of the treatment course. Since this study is conducted within an implementation framework it can easily be scaled up, and when successful, blended treatment has the potential to become an alternative offer in many outpatient clinics nationwide and internationally.

**Trial registration:**

Clinicaltrials.gov.: NCT04535258, retrospectively registered 01.09.20.

## Background

There is general agreement on what constitutes high quality treatment for alcohol use disorder (AUD). National and international clinical guidelines recommend the provision of evidence–based psychological treatment such as motivational interviewing (MI) and cognitive behavioral therapy (CBT) [1–3]. However, few people with AUD seek help for their problems and those who do tend not to seek treatment until several years after developing the disorder [4, 5]. Additionally, international studies show that people who seek help to curb their alcohol problem prefer treatment to be conducted outside conventional health care settings and opening hours [6, 7]. This is largely due to the shame and stigma attached to AUD, but also people may wish to deal with their problems on their own, lack knowledge about existing treatment options, or have poor access to treatment during day time because of family obligations, work, or geographic circumstances [8–10]. Since the treatment gap for AUD is considerable and there is evidence that compliance with AUD treatment is low, with high numbers of no shows and early dropouts [11, 12], this highlights the need for innovation in treatment delivery.

Introducing internet-based psychological treatment may be one way to minimize barriers to treatment delivery and increase access to evidence-based treatment for individuals with mental health problems like addictive disorders [7, 13, 14]. The potential benefits include ease of access (accessible 24/7 from different locations) and capacity to reach a wide range of users in a cost-efficient manner (due to less face-to-face time with the therapist) [15]. Internet-based psychological treatment is typically delivered as an interactive self-help program, comprising components such as symptom questionnaires, daily behavior monitoring with automated feedback, multimedia content, and exercises allowing users to practice coping skills [16, 17]. It can be delivered over a set time period as either 1) unguided Internet-based treatment: pure self-help programs that are not guided by a therapist; 2) guided internet-based treatment: more intensive programs that are guided online by a therapist; 3) blended treatment: consisting of online therapist-guided modules combined with face-to-face sessions.

Unguided internet-based self-help programs are considered useful for getting in contact with drinkers who avoid seeking traditional treatment due to fear of stigma, lack of knowledge about existing treatment options, or ambivalence about whether treatment is needed [7, 9], and such programs may lead to reduction in alcohol consumption in non-treatment-seeking/sub-clinical AUD samples [18–21]. However, although such programs are flexible and easy to access and use, non-compliance is a major challenge [18]. Hence, this type of intervention may primarily offer patients with AUD the opportunity to assess their drinking and degree of functionality, operating as a discrete information tool rather than as a treatment strategy per se. Guided internet-based programs, on the other hand, involve a certain level of contact with a therapist, typically in the form of text messages or emails. Such interventions may function as important and effective treatment strategies [22, 23]. Qualitative studies show that personal feedback and support are perceived positively by psychiatric patients, allowing them to use the program optimally and keeping them motivated [24, 25]. Further, several systematic reviews on the use of internet-based treatment for treating common mental health disorders have found that offering personal support and guidance during online treatment improves clinical outcomes and is associated with higher levels of treatment completion [23, 26, 27]. In addition, a large meta-analysis based on patient data from AUD treatment reported that guided internet-based treatment showed significantly better outcomes than unguided internet-based treatment [23].

A very recent study showed that unguided treatment may, in some cases, have a similar effect as guided treatment [28], but, overall, guided Internet-based treatment is the most promising.

A more novel approach, blended treatment, combines internet-based and face-to-face treatments into one integrated protocol [29–31]. Using this approach, part of the face-to face treatment is replaced by internet components, while the traditional face-to-face relationship between the therapist and patient is retained, thus adding an extra dimension to guided internet-based treatment. Including the face-to-face element ensures that patients benefit from a supportive therapeutic relationship, which is likely to increase motivation to complete treatment [32]. The Internet-based element, however, provides flexibility, allowing patients to access the treatment modules at the time and place of their choosing. Through an internet-based platform, therapists can give continuous feedback to patients and help them to stay on track with treatment [32, 33]. By extending access to treatment in terms of providing online sessions, the number of required face-to-face sessions can potentially be reduced, which may result in cost-savings [34]. However, studies are warranted addressing the clinical and cost-effectiveness of blended treatment.

Mental health care institutions are increasingly introducing blended treatment, and an evidence base has emerged demonstrating the clinical and cost-effectiveness of this type of treatment for a number of psychiatric disorders [14, 29, 31, 35–39]. Studies on the development and implementation of blended treatment for substance use disorders are still scarce [40]. In the context of AUD treatment, no studies have, to our knowledge, compared the effects of blended and traditional face-to-face treatments on a larger scale. This is despite the fact that many AUD patients, particularly those with more severe AUD, may benefit from combining face-to-face sessions with internet modules within the same treatment protocol [7, 41–43], thereby still involving face-to-face contact and making treatment easier to complete. Notwithstanding, blended treatment targeting AUD is currently offered at the Jellinek outpatient institutions in the Netherlands. The Jellinek blended treatment protocol is highly structured and based on evidence-based psychological treatment consisting of MI and CBT [1, 3], and both the clinical and implementation experiences have been positive. Further, a pilot-study testing this treatment program in three outpatient institutions in Denmark has shown promising preliminary results [44]. Therefore, the present large-scale study, “BLEND-A: Blending internet treatment into conventional face-to-face treatment for AUD”, was designed and developed.

The central aim of the BLEND-A Study is to examine and evaluate the effectiveness of the blended treatment program in an implementation framework allowing a country-wide upscale of AUD-treatment reach. We hypothesize that:
BLEND-A (internet-based modules combined with face-to-face outpatient treatment within the same protocol) will lead to a 10-percentage point better treatment compliance (primary outcome), measured as decreased premature dropout from treatment (dropout from treatment before planned conclusion), compared to TAU (face-to face outpatient treatment).BLEND-A will be more effective in reducing alcohol consumption (secondary outcome), measured via self-report 6 months after treatment intake, compared to TAUBLEND-A will lead to better quality of life (secondary outcome) 6 months after treatment start compared to TAU.BLEND-A will be a cost-effective treatment approach, comparable to face-to-face treatment (secondary outcome).

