#### Economic analyses

The economic analysis includes 1) cost comparisons, 2) a cost and benefits comparison, 3) a formal cost-effectiveness incremental cost-effectiveness ratio (ICER: ratio of Net Costs to Net quality-adjusted life-years (QALYs)), and 4) a business case analysis. Cost comparisons entail cost estimation of either of the interventions (BLEND-A or TAU), including costs that are directly related to the interventions and costs associated with the impact of the interventions on patients, i.e. health care utilization, social care, patients’ own resources and labor supply/productivity. Data on the use of resources will be extracted from population registries maintained by Statistics Denmark and The Danish Health Data Authority, and will be supplemented with data from the municipalities’ own databases and ad hoc measurements (especially for resources directly related to the interventions). Net costs, ∆C = (Costs(BLEND-A) minus Costs(TAU)), will be assessed with means, medians, and statistical tests, and decomposed into health net costs and social net costs. Prices and wage rates will be based on negotiated/market prices, DRG-rates and similar. Sub-group analyses will be performed for different patient categories.

Costs and benefits (premature dropouts, decreased alcohol intake, and increased quality of life at 6 months after treatment intake) in the two intervention groups will be compared and described to assess cost-effectiveness. A formal cost-effectiveness analysis will be performed according to international standards [63–65]. Validity of the EQ-5D, being a generic Quality of life (QoL) instrument, will be empirically assessed in the study by comparing EQ-5D measures with patient reported outcome (PRO) data. ICERs and sensitivity analysis will be estimated with non-parametric bootstrap-based confidence intervals.

Finally, we aim to perform a business case calculation using the Danish framework so that the municipalities can perform their own business cases to assess the consequences of implementing BLEND-A.

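### Alcohol consumption and quality of life have two incompatible follow-up times: six months after intake in the hypotheses and economic section, six months after treatment conclusion in the abstract and Table 1

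*Protocol article*

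**What the plan says.** Two places in the protocol article count from the beginning of treatment:

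- **Background, hypotheses 2 and 3.** Alcohol consumption is "measured via self-report 6 months after treatment intake". The third hypothesis is for "better quality of life (secondary outcome) 6 months after treatment start compared to TAU". Hypothesis 4, on cost-effectiveness, gives no time point.
- **Economic analyses.** The benefits to be set against costs include "increased quality of life at 6 months after treatment intake".

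Two places count from the end of treatment:

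- **Abstract, Methods.** Data "will be collected at treatment entry, at treatment conclusion, and 6 months after treatment conclusion". The abstract then says that "the secondary outcomes include alcohol consumption and quality of life at six-months follow-up". The only six-month assessment that it has described is the one after conclusion.
- **Table 1.** Alcohol consumption (AUDIT items), AUDIT and ADS severity, and EQ-5D are scheduled at "Treatment entry and 6-month follow-up post treatment". The SIP-2R row has a six-month follow-up but lacks the word that would fix its anchor.

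The Data collection text can be read either way. Patients are to "complete a questionnaire at treatment start and after treatment completion 6 months later". The paragraph that follows makes separate arrangements for patients who leave treatment ahead of the six-month assessment.

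**The concern.** An outcome is not defined until its time point is. Here two named secondary outcomes each have two, and both stand in current text. This is more than a detail that a journal article leaves to a fuller document, because the article states the time on both sides.

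The choice also changes what is measured. Intake is fixed before any treatment is received. Conclusion happens after randomisation, as either completion or dropout, and the type of conclusion is the primary outcome that the intervention is meant to change. If follow-up is counted from conclusion, the interval since baseline depends on how long a patient stayed, and so may differ between conditions. EQ-5D feeds the QALYs, so the economic comparison is exposed too. Leaving both definitions open also allows the anchor to be chosen after data are seen.

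**Working it through.** The article gives no figure to reproduce on this point. The check is calendar arithmetic on its own durations.

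**Inputs**

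- Usual treatment: typically 4 to 6 months (Treatment as usual).
- Active blended course: estimated at 3 months (BLEND-A treatment).
- Uptake of blended treatment once an institution has crossed over: 25–40% (Study design).
- Planned completion in 2014: 31% (Power calculations).

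**Step 1. Time from intake to follow-up for completers.** Counting from conclusion, time from intake = treatment duration + 6. Counting from intake, it is 6 for everyone.

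| Treatment received | Duration (months) | Conclusion anchor | Intake anchor | Difference |
|---|---|---|---|---|
| Blended | 3 | 3 + 6 = 9 | 6 | 3 |
| Usual, short | 4 | 4 + 6 = 10 | 6 | 4 |
| Usual, long | 6 | 6 + 6 = 12 | 6 | 6 |

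The difference between anchors equals the treatment duration, so the two coincide only at zero months. Counting from conclusion, completers of the two treatments are assessed 10 − 9 = 1 to 12 − 9 = 3 months apart.

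**Step 2. Shift between randomised conditions.** Institutions are randomised and the analysis is by intention to treat, so what matters is the mean over all patients in intervention periods, most of whom are expected not to use blended treatment. If non-users keep the usual duration and all patients complete, mean shift = uptake × (usual duration − 3).

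| Uptake | Usual treatment 4 months | Usual treatment 6 months |
|---|---|---|
| 25% | 0.25 × 1 = 0.25 | 0.25 × 3 = 0.75 |
| 40% | 0.40 × 1 = 0.40 | 0.40 × 3 = 1.20 |

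Among completers the shift is therefore about 0.25 to 1.2 months, with follow-up earlier in intervention periods.

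**Step 3. Patients who do not complete.** At 31% completion, 100 − 31 = 69% do not finish as planned; at the hypothesised 41%, 100 − 41 = 59% do not. For these patients the conclusion anchor starts at dropout. The article gives no distribution of dropout times, so this part of the shift cannot be calculated. A rise in completion, the effect being sought, would itself change the mix of follow-up times.

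**Step 4. Does the Data collection text decide?** Its main sentence can mean six months after start or six months after completion. The provision for patients who leave before the six-month assessment separates some patients from others only if that assessment can fall while treatment is still running. Counting from conclusion, every patient has already stopped by then and the provision would be empty. The text therefore fits intake better but does not say so.

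**The case against.** The strongest reply is that this is loose wording with a small consequence. The hypotheses, the economic section and the workable reading of the Data collection text all point to intake. Only the abstract and Table 1 clearly point elsewhere, and the primary outcome is taken from the register. Much of this stands: it is why the hypotheses should not be called untestable, and why most of the repair is editorial. It does not remove the conflict, because Table 1 is the article's assessment schedule.

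A second reply is that follow-up after conclusion answers a legitimate question about durability, and that an intake anchor has its own asymmetry. At month 6, completers of usual treatment are 6 − 6 = 0 to 6 − 4 = 2 months past planned conclusion, and completers of blended treatment 6 − 3 = 3 months. That is true, but time since baseline is then the same for everyone and does not depend on dropout.

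A reader might infer several stronger claims that the article does not support:

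- **That the arms are assessed 1–3 months apart.** That gap is between treatments received among completers. Uptake reduces it to about 0.25–1.2 months between randomised conditions.
- **That blended follow-up could fall at 15 months (3 + 6 + 6).** This counts the later relapse-prevention use of the platform as treatment, whereas the article places it after the active course. If it did count, the direction of the difference would reverse.
- **That the comparisons are biased by timing alone.** Any bias depends on the conclusion anchor being used, and no outcome trajectory is given from which to size it.
- **That costs and QALYs are planned over unequal horizons.** The economic section dates its benefits from intake, and resource use comes largely from registries that are not tied to the questionnaire date.

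**Conclusion.** The contradiction is real and should be resolved before analysis. It is an inconsistency in the timing of secondary outcomes. For completers the two definitions are 3 months apart (blended) or 4–6 months apart (usual treatment).

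If the conclusion anchor were used, the alcohol, EQ-5D and QALY comparisons would be at risk of timing bias. Among completers the mean shift between conditions is modest, about 0.25–1.2 months. That figure rests on durations the article calls typical or estimated, on 25–40% uptake, on non-users keeping the usual duration, and on everyone completing. The larger difficulty is the majority who do not complete, whose clock would start at an event that is the primary outcome. The size of that part is unknown. Register-based completion and the power calculation are not affected.

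**What to change.** Adopt one anchor, six months after the intake date, for the follow-up questionnaires (AUDIT, ADS, SIP-2R, EQ-5D) and for the cost and QALY horizon. Hypotheses 2 and 3 and the economic section already state this timing for the outcomes and benefits.

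- Correct the abstract and the follow-up entries in Table 1, and complete the SIP-2R row.
- Reword the questionnaire sentence in Data collection so that it counts from intake, and schedule the follow-up questionnaire from the intake date.
- If any questionnaires were collected on the conclusion clock (the article does not say), record the actual days since intake and report a sensitivity analysis restricted to a window around six months from intake. State how many patients the window excludes, by condition and by completion status, since on that clock it would mainly retain early leavers. Do not adjust the main model for days since intake: on that clock the interval arises after randomisation and reflects dropout.

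The cost is an edit to the protocol wording and, if scheduling currently runs from conclusion, a change to the questionnaire dates. Sample size and the primary analysis stay as they are.
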